### 2.4. Statistical Analysis

The primary efficacy analysis will be performed in the intention-to-treat (ITT) population. The pre-protocol population consisted of all patients in the ITT population without major protocol deviations and will be used for the supportive analysis of the primary efficacy endpoint.

The quantitative data collected, organized into two distinct groups of subjects, will be presented in tables that include the mean and standard deviation. In addition, qualitative data will be represented through frequency distributions.

The primary endpoint (number of MIGs/month from baseline to 6 and 12 months) will be analyzed using a linear mixed-effect model (LMEM) with treatment group × time as the fixed effect and the baseline number of MIG/month value as the covariate.

For qualitative data analysis, the Chi-square test will be implemented.

The scores obtained from the evaluation scales will be correlated with the clinical parameters of the participants, when applicable, using the Pearson or Spearman correlation coefficients, contingent upon the distribution of the data.

In the case of individuals with MIG, a logistic regression analysis will be performed to investigate potential associations between psychopathological parameters and the response to headache treatment. Adherence to both PA and TPE will be incorporated as process variables in the analyses. Dietary adherence scores from the Mediterranean Diet Assessment Tool, Diet Risk Score, and food-headache diaries will be assessed longitudinally for their potential as predictors of migraine outcomes. Additionally, EXE adherence will be evaluated through attendance records and wearable device data.

Analyses will be limited to participants with complete data on different measurements. We hypothesized that missing data occur randomly into two group. We plan to gather additional information from participants who drop out.

Should the dropout rate exceed our projections, we will employ a regression model to impute the missing data.

The exploratory outcomes will be evaluated utilizing the same LMEM employed for the primary analysis, without adjustments for multiple comparisons. Conclusions will be derived from effect size estimates, specifically Cohen’s d, accompanied by a 95% bootstrap confidence interval (CI). Effect sizes will be systematically classified as small (d = 0.2), medium (d = 0.5), and large (d = 0.8).

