All statistical analyses will be completed using IBM SPSS^®^ Statistics for Windows version 25.0 (IBM Corp., Armonk, NY, USA).

*Sample Size.* The sample size calculation was based on real-life data regarding the response rate to therapy through PA in people with MIG, specifically focusing on the number of headache days. According to the literature, this approach indicates a decrease of approximately 15–20% relative to baseline data [98]. To determine the number of participants in the intervention and control groups, we referenced various articles on the subject, particularly the work of Krøll et al. [98,99], which indicates that the average difference in the number of headache days is almost 2 days less than the baseline. The standard deviation is estimated to be approximately 50% of the average for both groups. Assuming a 1:1 ratio, with a significance level of 5% and a statistical power of 80%, a sample size of a total of around 200 participants (100 patients per group) will be determined, accounting for an anticipated dropout rate of 30%. The recruitment of this cohort will be scheduled for over 9 months to effectively achieve the desired enrollment.

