A limitation of this study is its unblinded design, as it is impossible in behavioral intervention research like EXE. Both participants and evaluators knew group assignments, which can introduce bias and potentially overestimate the intervention’s effectiveness. Participants in the intervention group, aware of receiving active treatment and engaging regularly with a kinesiologist, may have developed heightened expectations of improvement, potentially amplifying perceived reductions in pain and quality-of-life gains beyond the actual physiological effects of EXE (enhanced placebo effect). Conversely, control group participants, conscious of not receiving active intervention, may have experienced demoralization, contributing to reduced diary compliance, higher dropout rates, or an overestimation of symptom burden (e.g., demoralization). Furthermore, given the inherently subjective nature of pain assessment, intervention group participants may have been inclined to report more favorable outcomes to justify their investment in the treatment, introducing a degree of social desirability or reporting bias. Finally, the difference between the intervention and control groups likely stems from both the actual impact of exercise and psychological effects due to the lack of blinding, which may result in a larger reported effect size than in blind studies. Moreover, it is crucial to underline that our model will be initially applied to one center (the Headache Center of Perugia). This single-headache center recruitment may limit the study’s generalizability, as participants were drawn from a single clinical site, potentially introducing selection bias. This could affect the external validity of the results, as individuals at one center may not represent the broader migraine population. Future multicenter studies with diverse participants are needed to confirm and extend these findings.

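### The primary analysis is called intention-to-treat but is limited to participants with complete data, with imputation only above 30% dropout

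*Protocol article*

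**What the plan says.** Four statements in section 2.4 of the protocol article bear on who enters the primary analysis:

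- **Population:** "The primary efficacy analysis will be performed in the intention-to-treat (ITT) population". A per-protocol set is reserved for supportive analysis.
- **Model:** the primary endpoint, at 6 and 12 months, "will be analyzed using a linear mixed-effect model (LMEM) with treatment group × time as the fixed effect", with the baseline count as covariate.
- **Restriction:** "Analyses will be limited to participants with complete data on different measurements". The support offered is "We hypothesized that missing data occur randomly into two group".
- **Imputation:** "Should the dropout rate exceed our projections, we will employ a regression model to impute the missing data".

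The projection is in the sample-size paragraph of the same section: about 200 participants, "accounting for an anticipated dropout rate of 30" per cent. No rate per arm is given.

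The Discussion, on the limits of the unblinded design, says that control participants "may have experienced demoralization, contributing to reduced diary compliance, higher dropout rates".

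**The concern.** The population statement and the restriction cannot both govern the primary endpoint. An intention-to-treat analysis keeps randomised participants in their allocated arms. A complete-data analysis removes those with a missing visit. If the restriction applies, the analysis labelled intention-to-treat is a completer analysis.

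The restriction also undoes the main advantage of the chosen model. A likelihood-based mixed model can use a participant who has a 6-month value but no 12-month value. It is valid when missingness depends on observed quantities such as arm, baseline and the 6-month count.

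The imputation clause does not rescue the plan. It starts only when dropout is worse than projected, so at the projected rate the completer analysis stands. It also lets the observed dropout rate decide which method produces the primary result.

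The assumption of random missingness sits badly with the Discussion. The trial is unblinded and attack counts come from participants' diaries, so the mechanism named there, demoralised controls keeping fewer diaries or leaving, acts directly on the primary outcome.

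**Working it through.** **1. How many could be excluded.** Imputation applies only above 30% dropout. 0.30 × 200 = 60 randomised participants can be missing before it starts.

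**2. Inputs for an illustration of bias.**

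- From the documents: 100 per arm; visits at baseline, 6 and 12 months; planning effect of about 2 days, said to be 15–20% of baseline; SD about 50% of the mean.
- Derived: at 20%, mean = 2/0.20 = 10 and SD = 0.5 × 10 = 5. At 15%, mean = 13.3 and SD = 6.7. SD 5 is used below; the biases scale in proportion to the SD.
- Assumed, because the documents give no figure: no true effect; all dropout after month 6; about 40–41% dropout in controls and 20–21% in the intervention arm, so about 30% overall; correlation 0.6 between the two follow-up visits and 0.5 or 0.6 between each of them and baseline.
- Outcome-dependent dropout, with z = (6-month value − mean)/SD: logit(p) = −0.45 + z in controls. In the intervention arm, either logit(p) = −1.6 + z (same dependence) or a flat 20%.

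**3. Estimators**, over 4,000 simulated trials per case. Complete-case: baseline-adjusted difference among those with both visits. All observed data: at month 6, the same regression on everyone; at month 12, the likelihood estimate that combines the 6-month regression on everyone with the 12-month regression on completers.

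**4. Results.** Bias in days, intervention minus control; positive is against the intervention. Ranges cover baseline correlation 0.6 to 0.5.

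| Dropout after month 6 | Complete-case, month 6 | Complete-case, month 12 | All observed data, both visits |
|---|---|---|---|
| Unrelated to outcome, 40% v 20% | about 0 | about 0 | about 0 |
| Same dependence in both arms, 41% v 21% | 0.5–0.6 | 0.2–0.3 | about 0 |
| Same dependence, 30% in each arm (correlation 0.6 only) | about 0 | about 0 | about 0 |
| Only control dropout depends on outcome, 41% v 20% | 1.1–1.3 | 0.4–0.6 | about 0 |
| Only intervention dropout depends on outcome, 20% v 41% (correlation 0.6 only) | −1.1 | −0.4 | about 0 |

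Against the 2-day planning effect, 1.1/2 = 55% and 1.3/2 = 65%. The last row shows that the sign depends on who leaves.

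**5. Precision.** With 40% v 20% dropout unrelated to outcome, 60 and 80 participants remain. The standard error at month 6 should rise by √[(1/60 + 1/80)/(1/100 + 1/100)] = √(0.02917/0.02) = 1.21. The simulation agrees at correlation 0.6: 0.57 rises to 0.69.

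**6. What the all-data model cannot do.** In a separate run of 2,000 trials (true effect 2 days, follow-up correlation 0.7, baseline correlations 0.6, control dropout dependent on the unobserved 12-month value), bias at month 12 was 1.1 days for complete cases and 0.8 days with all observed data.

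**The case against.** Several points on the other side stand.

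- A reader might infer that the protocol expects dropout to differ by arm. It does not say so. The Discussion says controls may drop out more, as a limitation and without a rate. The only planning assumption is random missingness with a single 30% figure.
- A reader might infer that the two sections flatly contradict each other on missingness. Random missingness could mean random within each group, which is compatible with unequal rates. The Discussion does not say whether the participants who leave are the worse-off ones. The tension is real but falls short of a contradiction.
- Unequal dropout alone does not bias the estimate, as the first row of the table shows. Bias needs dropout that is related to outcome beyond baseline and that acts differently by arm.
- The larger biases need all dropout to fall after month 6. Anyone who leaves earlier has no post-baseline value to recover, so the change gains less for them.
- Complete data may mean complete for each measurement, not for every instrument at once. The documents do not settle this. The milder reading keeps more participants but still removes any randomised participant without the needed visits.
- The article plans to gather information from people who drop out, and it does have an imputation clause. Neither applies to the primary estimate at or below 30% dropout.
- Sensitivity analyses are commonly left to an analysis plan that is not shown, so their absence here is not an error.

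None of this removes the conflict between the population statement and the restriction. The article states the rule, so it is not a detail left out for brevity.

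**Conclusion.** The point holds as a conflict in the stated rules. The primary analysis is called intention-to-treat, yet the text restricts it to complete data. At the projected dropout, up to about 60 of 200 randomised participants could be excluded with no imputation, and usable 6-month values would be lost. That conclusion rests on the text alone and is firm.

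The effect on the estimate is conditional. The restriction loses precision and can bias the treatment difference; it need not. Under the assumed inputs the bias at month 6 runs from about 0 to 1.3 days, and at month 12 from about 0 to 0.6 days, in either direction depending on which arm loses its worse-off participants. No single figure should be quoted as the bias, because every dropout input is an assumption.

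The conflict should be resolved before analysis, because as written it leaves the primary population undetermined.

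**What to change.** 1. Delete the complete-data restriction for the primary analysis.
2. State that the mixed model is fitted to all randomised participants in their allocated arms, using every available post-baseline value, under missing at random given arm, baseline and earlier visits.
3. Remove the switch to regression imputation that depends on observed dropout, or make it a pre-specified sensitivity analysis that is run whatever the dropout rate.
4. Label any completer analysis as supportive.
5. Advisable, and suited to the analysis plan: one delta-adjusted sensitivity analysis with shifts set separately by arm, because the all-data model does not remove bias when dropout depends on unobserved values.

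The cost is a few sentences of wording and one extra analysis run. No change to data collection or sample size is needed for this point.

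### The missing-data method changes once dropout passes the projected 30%, and the complete-data default below that line conflicts with the intention-to-treat mixed model

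*Protocol article*

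**What the plan says.** All of this is in section 2.4 (Statistical Analysis) of the protocol article.

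- Population: "The primary efficacy analysis will be performed in the intention-to-treat (ITT) population".
- Primary model: the endpoint at 6 and 12 months "will be analyzed using a linear mixed-effect model (LMEM) with treatment group × time as the fixed effect", with the baseline value as covariate.
- Default for missing data: "Analyses will be limited to participants with complete data on different measurements".
- Assumed mechanism: "We hypothesized that missing data occur randomly into two group".
- Switch: "Should the dropout rate exceed our projections, we will employ a regression model to impute the missing data".
- The projection, in the Sample Size paragraph: about 200 participants, "accounting for an anticipated dropout rate of 30" per cent.

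The section does not say whether the imputation is single or multiple, how results would be pooled, or whether the imputed analysis would replace the primary analysis or support it.

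**The concern.** There are two problems in what is written and one in what the wording permits.

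First, whether a missing-data method is valid depends on why values are missing, not on whether dropout ends just below or just above 30%. Because 30% is the expected rate, the trial may well finish close to the line. The rule does not tie the rate to an arm or a visit, although the endpoint uses two visits and the Discussion says that evaluators know the allocation.

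Second, restricting to complete data removes randomised participants from an analysis declared as intention to treat. It also discards the 6-month value of anyone who leaves before 12 months. The mixed model does not need this, because it uses all available follow-up under missing at random. The Discussion itself raises possible demoralisation and higher dropout among controls, so an analysis of completers is a poor default.

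Third, if imputation means one filled-in value per missing outcome, the filled-in values are counted as observations and the primary confidence interval and p-value would be falsely precise.

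**Working it through.** **The plan's own figure.** 30% of 200 is 60 dropouts, leaving 140 completers (70 per arm). The trigger is therefore more than 60 dropouts, if the rate is taken overall.

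**What the complete-data default discards.** Suppose, as an illustration, that half of the 60 dropouts leave after the 6-month visit. Then 0.5 × 60 = 30 participants have a usable 6-month value. The mixed model would use these values, and a complete-data restriction would drop them.

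**What single imputation would do.** Inputs: N = 200 (Sample Size paragraph) and fraction missing m = 31%, 35% or 40% (just above the trigger and beyond). Assumptions: values missing completely at random, no true effect, one follow-up visit, ANCOVA on baseline, and imputation from arm and baseline.

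*Deterministic fill-in.* Imputed values lie on the fitted line, so the estimate and the residual sum of squares are those of the n = N(1 − m) observed cases. The analysis nevertheless divides by N − 3 instead of n − 3 and credits information from N people. Hence:

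reported SE / true SE ≈ √[((n − 3)/(N − 3)) × (n/N)] ≈ 1 − m

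At m = 0.31, n = 138: √[(135/197) × (138/200)] = 0.69.

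Type I error ≈ 2[1 − Φ(1.96(1 − m))].

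*One random draw.* The true variance is proportional to 1/(1 − m) + m, while the reported variance is proportional to 1. At m = 0.31 the SE ratio is 1/√(1.449 + 0.31) = 0.75, and type I error ≈ 2[1 − Φ(1.96 × 0.754)] = 13.9%.

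The approximations agree with simulation (100 per arm; assumed baseline–outcome correlations 0.3, 0.5 and 0.7; 3,000 null trials per setting for the simulated columns below):

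| Missing | Deterministic, formula | Deterministic, simulated | One draw, formula | Observed cases, simulated | Multiple imputation (20 sets, Rubin), simulated |
|---|---|---|---|---|---|
| 31% | 17.6% | 16.9–18.8% | 13.9% | 4.5–5.5% | 4.0–5.4% |
| 35% | 20.3% | 20.0–20.6% | 15.4% | 5.1–5.2% | not run |
| 40% | 24.0% | 24.3–25.1% | 17.3% | 4.9–5.5% | 4.5–5.4% |

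Simulated one-draw imputation gave 14–17% over the same 31–40% range. In simulation, the deterministic SE was 0.67–0.70 of its true value at 31% missing and 0.59 at 40%, that is 30–41% too small. Multiple-imputation SEs were within about 1–1.5% of the complete-case SE.

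**Across the line.** Take 29% against 31% dropout as an illustration: 142 against 138 completers. The honest SE rises by √(142/138) = 1.014, or 1.4%. With deterministic single imputation above the line, the reported SE would be 0.69 × 1.014 = 0.70 of its value just below. Losing four more participants would make the result look about 30% more precise.

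**Two visits.** The plan has two follow-up visits. Assume 31–40% missing by month 12, half of the dropouts leaving after month 6, baseline correlation 0.5 and between-visit correlation 0.5–0.8. Simulated type I error with single imputation, tested by ANCOVA, was then:

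| Test | Deterministic | One draw |
|---|---|---|
| Month 6 | 10–13% | 8–11% |
| Month 12 | 14–23% | 11–17% |
| Average of both | 11–15% | 9–12% |

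**The case against.** The strongest reply is that the text never says single imputation. Multiple imputation also uses a regression model, and a journal article may leave the number of imputations and the pooling to the full plan. This stands. A reader might infer that the standard errors will be too small and the primary p-value invalid, but the document does not support that as a fact. It is true only if single imputation is meant.

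A reader might also infer that a rule triggered by the data inflates type I error by itself. That is not supported either. The rule is written in advance, and its trigger is dropout rather than the treatment effect.

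It can be said that the imputation sentence is not tied to the primary endpoint. That is true, but neither that sentence nor the complete-data restriction exempts the primary endpoint, and both stand in the section that defines it.

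Nor would imputation start only when most values are missing: the trigger is anything above 30%. Finally, the one-visit figures lie towards the top of the range, and two visits give less inflation at month 6 and for the average.

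None of this removes the switch or the conflict with intention to treat. Both are in the text and would remain whatever a fuller plan adds about imputation.

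**Conclusion.** The point holds in two parts.

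Without further assumption: section 2.4 fixes two missing-data methods, lets observed dropout choose between them, and sets as default a complete-data restriction that conflicts with the declared intention-to-treat analysis and gives up the main advantage of the mixed model. That 30% is the trigger is an inference from the Sample Size paragraph, where it is the only projection given.

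Conditionally: if the imputation is single, type I error at nominal 5% would be about 17–25% (deterministic) or 14–17% (one draw) with 31–40% missing. This rests on missingness completely at random, one visit, ANCOVA and assumed correlations of 0.3–0.7, across which the results hardly varied. With two visits it is probably lower at 6 months and for the average. If the imputation is proper multiple imputation, the error stays near 5%.

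The text should be changed under either reading.

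**What to change.** For the primary endpoint, delete the dropout trigger and the complete-data restriction. State that, whatever the dropout rate, the planned mixed model is fitted to all available 6- and 12-month data from all randomised participants. State that any imputation is multiple, done by arm with baseline and earlier visits as predictors, pooled by Rubin's rules, and serves as a prespecified sensitivity analysis.

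The cost is protocol wording and a little computing. No additional participants, visits or measurements are needed.

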### 2.2. Project Phases

#### 2.2.1. Phase 1: Enrollment and Medical Assessment

All participants will be invited to attend their first specialist visit to the Headache Center of the Santa Maria della Misericordia Hospital in Perugia. The neurologist conducts a thorough interview covering the onset and evolution of the headache, its frequency, duration, and intensity, associated symptoms (nausea, vomiting, photophobia, phonophobia), presence of aura, triggering and relieving factors, family history, sleep quality, stress levels, and menstrual cycle in women.

During the neurological assessment, we will collect comprehensive information for each participant, including age, sex, age of headache onset (in years), potential onset of MIG chronicity (in years), existing comorbidities, other medications being utilized, and symptomatic medications used as needed (with a focus on their efficacy). Furthermore, we will gather details regarding prophylactic medications (usage timing, dosage, potential side effects, and effectiveness: yes/no assessed as a reduction of at least 50% of attacks after at least 3 months of treatment compared to the pre-treatment period) along with the characteristics of the headaches (presence of aura, occurrence of other primary headaches, and frequency of headaches experienced in the past three months). Moreover, blood test results and any previous neuroimaging are reviewed to exclude secondary causes of headache and to assess comorbidities relevant to treatment decisions.

Based on all collected data, the neurologist formulates a diagnosis following the International Classification of Headache Disorders (ICHD-III, 2018) [53], distinguishing between migraine (with or without aura), chronic migraine (≥15 headache days/month for >3 months), tension-type headache, medication overuse headache, and other primary or secondary headache disorders. The neurologist also formulates a personalized treatment plan including acute medications, preventive pharmacological therapy (e.g., beta-blockers, antiepileptics, calcitonin gene-related peptide (CGRP) monoclonal antibodies), and non-pharmacological strategies (lifestyle modifications, biofeedback, physical therapy referral). During this phase, participants will receive detailed information about the project, and an informed consent form, along with a data processing form, will be presented for their signature.

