## 3. Expected Results

As this is a study protocol, no actual results are currently available. The following section outlines the study’s hypotheses and anticipated outcomes based on existing evidence. According to the current literature, the proposed interdisciplinary intervention, primarily based on supervised physical EXE and TPE, is hypothesized to improve clinical outcomes in individuals with MIG (e.g., frequency) and may also contribute to improvements in lifestyle-related outcomes and overall disease burden [100].

Regarding the primary outcome, the study aims to evaluate whether the intervention is associated with a reduction in MIG frequency. It is hypothesized that the intervention group may show a decrease in monthly headache days of approximately 15–20% compared with baseline [98]. This assumption is in line with previous evidence, including studies by Krøll et al. [98,99], which reported an average reduction of about two headache days per month in people engaging in PA interventions.

Regarding the secondary outcomes, in accordance with previous studies [14,17,62], we hypothesize that the intervention may be associated with improvements in MIG-related disability, MSQoL, MIG intensity, PA levels, and sedentary behavior, medication use (number of doses/month), dietary adherence, functional capacity, and postural and temporomandibular function, in line with the intervention’s interdisciplinary nature [101]. With respect to explorative measures, potential improvements may be observed in sleep quality [102], weight and WC [103,104], and key cardiometabolic parameters (including fasting glucose, HbA1c, lipid LDL, HDL, triglycerides, blood pressure, and CRP) and related risk, which may reflect changes in systemic inflammation and cardiometabolic risk, particularly among participants in the supervised EXE program [105,106]. However, these outcomes will be explored and require confirmation.

Additional benefits are anticipated in other areas, including anxiety and depression symptoms, and kinesiophobia. A reduction in allodynia scores is also hypothesized, suggesting a potential modulation of central sensitization mechanisms [107].

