For the previous considerations, an interdisciplinary approach, involving professionals such as neurologists, dieticians, kinesiologists, and gnathologists, allows for a more comprehensive assessment and may act on multiple aspects relevant to MIG management. This approach could promote greater treatment adherence, reducing dependence on medication and improving quality of life, laying the foundation for stable and lasting change in the lifestyle of individuals with MIG. In this context, TPE serves as a crucial resource for enhancing people’s awareness. It encourages individuals to recognize their specific triggers and fosters the development of self-management skills [126,127]. Our protocol is designed to evaluate whether a reduction of approximately 15–20% in monthly attacks and improvements in clinical metrics can be achieved. The goal is not only to achieve immediate clinical benefits but also to encourage long-lasting lifestyle changes among participants.

Additionally, our study could contribute to the development of a potentially replicable interdisciplinary model that can be applied in headache centers and in general medicine and rehabilitation settings. It also aims to promote the implementation of the EXE recommendations. However, there are potential limitations to consider.

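### The sample size rests on a fall from baseline in people who exercise, while the primary analysis compares two arms; no between-arm difference or control-arm change is stated

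*Protocol article*

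**What the plan says.** Two effect figures are given in the Sample Size paragraph of section 2.4, both measured against baseline: "a decrease of approximately 15–20% relative to baseline data" and a reference to earlier work, "which indicates that the average difference in the number of headache days is almost 2 days less than the baseline". The SD is put at about half the mean in both groups. Allocation is 1:1, "with a significance level of 5% and a statistical power of 80" percent, and the total is about 200, said to allow for 30% dropout.

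Section 3 (Expected Results) shows whose change this is. The percentage is a hypothesis that "the intervention group may show a decrease in monthly headache days of approximately 15–20% compared with baseline". The two days come from studies that "reported an average reduction of about two headache days per month in people engaging in PA interventions". The Discussion repeats the figure as a design goal: "Our protocol is designed to evaluate whether a reduction of approximately 15–20% in monthly attacks" can be achieved.

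The planned comparison is a different quantity. Section 2.4 analyses the primary endpoint with a linear mixed model containing treatment group × time and baseline as covariate. The Abstract's conclusion states the question as exercise and education added to standard care against standard care alone. The article gives no expected control-arm change and no expected difference between arms.

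**The concern.** Power has to refer to the contrast that is tested. If the exercise arm falls by 2 days and controls fall by c days, the contrast is 2 − c. Entering 2 amounts to assuming c = 0.

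The article itself gives reasons to doubt c = 0:

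- Section 2.1 selects people with high current frequency (8–14, or at least 15, attacks a month), so some regression to the mean can be expected in both arms.
- Section 2.2.1 says of the enrolment visit, which precedes randomisation: "The neurologist also formulates a personalized treatment plan including acute medications, preventive pharmacological therapy".
- Section 2.2.2 gives everyone a food-headache diary, meant to help identify and avoid triggers, and a nutrition brochure.

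At stake is whether the stated 80% power applies to the question the trial asks. If it does not, a real but smaller benefit of exercise over standard care could easily be missed.

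**Working it through.** **Inputs**

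- From section 2.4: effect 2 days; 15–20% of baseline; SD about 50% of the mean; alpha 5%; power 80%; 1:1; 30% dropout; 100 per group.
- Inferred: if 2 days is 20% of baseline, the baseline mean is 2 / 0.20 = 10 and the SD is 0.5 × 10 = 5. If it is 15%, the mean is 2 / 0.15 = 13.3 and the SD is 6.67.
- Assumed: two-sided test (sidedness is not stated); no baseline adjustment; control improvement c of 0, 0.5 or 1 day (the article gives none).

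**Step 1. Reproduce the plan's figure.** The number per arm is n = 2(1.960 + 0.842)² SD² / δ².

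- δ = 2, SD 5: 2 × 7.849 × 25 / 4 = 98.1, so 99 per arm. This matches 100 per group, but only before dropout; with 30% dropout it is 99 / 0.7 = 142.
- δ = 2, SD 6.67: 175 per arm, or 251 with dropout.

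The stated total including dropout is therefore not reproduced on the plain two-sided reading. It appears only with additions such as a one-sided test or a baseline correlation of about 0.55. The match at 99 is consistent with the 2-day fall having been used as the between-arm difference; it does not prove it.

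**Step 2. Isolate this problem from the dropout shortfall.** Use 100 analysed per arm and SD 5, where δ = 2 gives the planned power. The standard error of the difference is 5 × √(2/100) = 0.707, and power ≈ Φ(δ / SE − 1.960).

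| Control improvement | Difference δ | δ / SE | Power |
|---|---|---|---|
| 0 day | 2.0 | 2.83 | 80% |
| 0.5 day | 1.5 | 2.12 | 56% |
| 1 day | 1.0 | 1.41 | 29% |

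**Step 3. Repeat under a favourable SD.** Take SD 4.18, at which 70 evaluable per arm (100 less 30%) give 80% power for 2 days. This is also what SD 5 becomes after adjustment at a baseline correlation of 0.55: 5 × √(1 − 0.55²) = 4.18. The standard error is 4.18 × √(2/70) = 0.707, so power is again 80%, 56% and 29%.

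**Step 4. Number needed for 80% power at SD 5.** For δ = 1.5, 2 × 7.849 × 25 / 2.25 = 174.4, so 175 per arm analysed. For δ = 1, 2 × 7.849 × 25 / 1 = 392.4, so 393 per arm analysed.

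**The case against.** Several points on the other side have force.

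- **Control change is not documented.** The shared treatments go to both arms. If the 2 days were the effect of physical activity alone, already net of other change, shared improvement would cancel. Section 3 reads otherwise, as the reduction seen in people who exercise, but the cited studies cannot be checked here. If they report a difference against controls, the sponsor need only say so. The Discussion also warns that unblinded controls may be demoralised and overstate symptoms, which would widen the reported difference. Control improvement is therefore likely, not certain, and its size is unknown.
- **Baseline adjustment helps.** The mixed model carries the baseline covariate, which lowers the residual variance and recovers some power. No correlation is stated, and adjustment does not turn a within-arm change into a treatment effect.
- **Dropout is a separate matter.** With 70 per arm and SD 5, power is about 65% even if controls do not change. That loss comes from the dropout allowance and the SD, and is not counted here.

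A reader might go further and infer that the trial cannot separate exercise from standard care, because a 15–20% fall would meet its aim even if controls fell as much. The article does not support that. The Abstract states the aim against standard care alone, section 2.4 plans a between-arm analysis in the intention-to-treat population, and the 15–20% in the Abstract and section 3 is a hypothesis rather than a success criterion. Only the Discussion sentence is worded loosely as a goal.

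**Conclusion.** The point holds for the sizing input. The only effect given is a change from baseline in people who exercise, so the 80% power is stated for a quantity that the primary analysis does not test. The plan implicitly needs zero control-arm change and does not say or justify this.

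If controls improve and the 2 days is the exercise arm's total fall, the planned difference is too large by the amount of that improvement. How much this costs cannot be fixed from the article. Half a day of control improvement would take power from 80% to 56%, and one day to 29%, under the SD, sidedness and analysed numbers assumed above. The analysis and the stated aim are already between-arm and are not at fault.

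**What to change.** In the Sample Size paragraph of section 2.4:

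- State the target as the intervention-minus-control difference in mean change in the primary outcome, at the time point or points used for sizing (6 months, 12 months or both).
- Give the assumed control-arm change, the SD in days and any baseline correlation relied on.
- Restate power for the planned enrolment over a range of control change, for example 0, 0.5 and 1 day.

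In the Discussion, reword the goal so that benefit is judged on the between-arm difference with its 95% confidence interval. In the Abstract and section 3, it is enough to mark the 15–20% as an expected within-arm change.

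The cost is wording and a less favourable stated power. No extra enrolment and no change to procedures is asked for. Rewording does not restore power; it makes clear what 200 participants can and cannot detect.
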